**Figure 1 fig1:**
[figure not shown]
Study flowchart. Reasons for inclusion and exclusion of patients are detailed in Materials and Methods section. ACS, acute coronary syndrome; MACE, major adverse cardiac event.

Patients with the following conditions are excluded: (1) patients unable to understand the research requirements or refuse to sign the informed consent form; (2) patients with unstable clinical status (e.g., hemodynamics or ECG instability); (3) patients with uncontrolled arrhythmia, defined as recurrent or symptomatic ventricular tachycardia and atrial fibrillation with rapid ventricular reaction that the drug cannot control within 3months prior to screening; (4) patients with severe renal insufficiency, defined as the estimated glomerular filtration rate (eGFR)<30ml/min/1.73m^2^; (5) patients with active liver diseases or liver dysfunction, either recorded in the patient’s medical record or defined as an increase in aspartate aminotransferase (AST) or alanine aminotransferase (ALT) more than 3 times above the upper limit of normal range; (6) patients with intolerance to rosuvastatin (any dose) or to other statins; (7) patients with known allergies to contrast agents, heparin, aspirin, ticagrelor, or clopidogrel; (8) patients with known allergies to supplements required for the use of the drug; (9) patients who have been treated with evolocumab or other PCSK9 inhibitors; (10) patients who have received cholesterol ester transfer protein inhibitors treatment 12months prior to screening; (11) patients who have received systemic steroid or cyclosporine treatment in the past 3months; (12) patients with known infections, hemorrhages, metabolic or endocrine disorders as determined by the researchers; (13) patients who have been included in other studies; (14) patients with active malignant tumor in need of treatment; and (15) women who are fertile (age<50years, menstruation in the past 12months) and have not received tubal ligation, oophorectomy, or hysterectomy.

### Data Collection and Management

Data will be recorded in Case Report Forms (CRFs) and entered into the clinical trial center by an electronic data capture system. Baseline data and data of different follow-up time points will be recorded. The schedule for the baseline assessment and subsequent assessments at different follow-up time points is shown in Table 1. Researchers on the trial management team will ensure the completeness and accuracy of the data. The trial manager, principal investigator, statisticians, and other members of the trial team will review the data cooperatively and complete the final definition and judgment of population analysis. The database will be secured.

**Table 1 tab1:** Schedule of treatments and assessments administered to patients.

Research stage	Screening stage	Follow-up treatment stage															
Visit (V)	V1	V2			V3	V4	V5	V6	V7	V8	V9	V10	V11	V12	V13	V14	V15
Date (D)	D-3 to D0	D1	D2	D3	D7	D14	W4 ± 3	W6 ± 3	W8 ± 3	W10 ± 3	W12 ± 3	W16 ± 3	W20 ± 3	W24 ± 3	W32 ± 3	W40 ± 3	W48 ± 3
Visit window																	
Inclusion/exclusion criteria	✓	✓															
Informed consent	✓																
Medial history	✓																
^*^Evolocumab treatment	✓																
Physical examination^(1)^	✓																
Vital signs^(2)^	✓	✓															
Blood routine^(3)^	✓				✓		✓				✓			✓			✓
Cardiac enzymes^(4)^	✓				✓		✓				✓			✓			✓
Blood lipids^(5)^	✓				✓		✓				✓			✓			✓
Blood sugar	✓				✓		✓				✓			✓			✓
hemoglobin A1c	✓						✓				✓			✓			✓
Liver function and renal function^(6)^	✓				✓		✓				✓			✓			✓
D-dimer	✓				✓		✓				✓			✓			✓
Uric acid	✓				✓		✓				✓			✓			✓
NT-proBNP	✓				✓		✓				✓			✓			✓
Thyroid function^(7)^	✓						✓				✓			✓			✓
High-sensitivity C-reactive protein	✓				✓		✓				✓			✓			✓
Ultrasound cardiogram	✓						✓				✓			✓			✓
PROMIS 10	✓										✓						✓

* Evolocumab is administered once every 2weeks.

(1) Physical examination: height and weight.

(2) Vital signs: body temperature, blood pressure and heart rate.

(3) Blood routine: RBC, WBC, platelet, and hemoglobin.

(4) Cardiac enzymes: creatine kinase (CK), CK-MB, troponin T (TnT), and Troponin (TnI)

(5) Blood lipids: low-density lipoprotein cholesterol (LDL-C), high-density lipoprotein cholesterol (HDL-C), very low-density lipoprotein cholesterol (VLDL-C), total cholesterol, triglycerides, apolipoprotein B, apolipoprotein A-1, lipoprotein (a), and free fatty acids.

(6) Liver function and renal function: aspartate aminotransferase (AST), alanine aminotransferase (ALT), alkaline phosphatase (ALP), γ-glutamyltransferase (γ-GT), acetylcholinesterase, mitochondrial isoenzymes, total bilirubin, creatine, and estimated glomerular filtration rate (eGFR)

(7) Thyroid function: thyroid-stimulating hormone (TSH), thyroid hormones, and triiodothyronine.

### Baseline Assessments and Laboratory Examinations

At baseline, the following characteristics are assessed: (1) demographic characteristics (gender, date of birth), (2) physical status (height, weight, body temperature, blood pressure, heart rate), (3) medical history (hypertension, diabetes, hyperlipidemia, heart disease history, peptic ulcer, stroke history), (4) treatment history (coronary heart disease, names of drugs used), (5) family history (hypertension, diabetes, coronary heart disease, hyperlipidemia, stroke), (6) life style (smoking, drinking), (7) current medical history, (8) echocardiography (left atrium, left ventricle, left ventricular ejection fraction, pulmonary artery pressure), and (9) laboratory examinations.

The laboratory examinations will be performed at baseline and at weeks 1, 4, 12, 24 and 48 post-treatment and will include the following: routine blood tests [blood glucose, liver function panel [albumin, total and direct bilirubin, alkaline phosphatase, aspartate aminotransferase, alanine aminotransferase], kidney function panel (serum creatinine, blood urea nitrogen)]; serum lipids panel [LDL-C, non-HDL-C, total cholesterol, triglycerides, apolipoprotein B, apolipoprotein A1, lipoprotein(a)]; myocardial damage markers [serum creatine kinase (CK), CK-MB, troponin I (TnI), and troponin T (TnT)]; and quality of life assessment using the PROMIS 10 scale (a Global Physical Health Score and a Global Mental Health score; Cella et al., 2007).

### Treatment Procedures Records

Treatment-related procedures will be recorded, including all medication used; percutaneous coronary intervention (PCI), coronary artery bypass (CABG) or thrombolytic therapy for revascularization, coronary angiography of the diseased vessels (e.g., left anterior descending artery, left circumflex artery, left main artery, right coronary artery, tunneled artery), stent implantation factors (target vessels for stent implantation, number of stents, stent diameter, stent length, stent overlapping); and postoperative lesions (degree of residual diameter stenosis, thrombolysis in myocardial infarction (TIMI) grade flow).

### Main Outcome Measures

Subjects of the present study will receive 24 treatments after being enrolled, and data of laboratory examinations will be evaluated at 72h and weeks 1, 4, 8, 12, 24, and 48 after intervention (Table 1; Figure 1).

The primary outcome of the present study will be the mean percentage change of the LDL-C level between baseline and weeks 4 and 12 post-treatment (Table 1; Figure 1). The secondary outcome will be MACE (defined as coronary heart disease death, nonfatal myocardial infarction, hospitalization for unstable angina, unplanned coronary revascularization, and stroke) assessed at week 12 and week 48 post-treatment (Table 1; Figure 1). The following issues will also be investigated: (1) the proportion of patients with LDL-C<70mg/dl, <55mg/dl and<40mg/dl during the study period; (2) patients’ quality of life as evaluated with the PROMIS 10 scale at week 12 and week 48 post-treatment; and (3) the percentage change in inflammatory biomarkers including but not limited to high-sensitivity C-reactive protein (hsCRP), interleukin (IL)-1β and IL-6, from baseline to weeks 48 (Table 1; Figure 1). Other biomarkers that exhibit significant difference between the two study arms will be investigated retrospectively after the trial.

### Safety Evaluation

For safety outcome analysis, missing data will not be imputed. Adverse events (AEs) will be recorded and summarized using descriptive statistics. Tolerability of study drug will be monitored and evaluated throughout the study period *via* regular medical examination and laboratory tests. For analyses of clinical endpoints, incidence of AEs and/or serious adverse events (SAEs) will be summarized for each randomized treatment group. Serious adverse events include cardiovascular events (death, fatal or non-fatal MI, coronary revascularization, hospitalization for recurrent ACS, hospitalization for heart failure, stroke, transient ischemic attack), muscle-related adverse events, neurocognitive impairments, incident diabetes; adverse events of special interest include allergies, injection-site reactions, or any other clinical abnormalities. If unexpected or SAE occur, the researchers or staff will fill out the SAE Report Form and notify the Ethics Committee and the State Food and Drug Administration (SFDA) as well as the pharmacological authorities.

Possible intervention-related complications will be recorded at 72h, and weeks 1, 4, 8, 12, 24, and 48 after intervention, including: dissection, acute thrombosis, coronary perforation, puncture site complications, allergic reactions, vasovagal response, perioperative myocardial infarction, cerebrovascular events, and hypotension.

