Statins have been widely used as an effective LDL-C lowering agent for ASCVD patients (Wang et al., 2017; Fox et al., 2018). However, many patients are unable to achieve the recommended LDL-C goal after high-intensity statin therapy (Wang and Fang, 2018). In addition, statins have the disadvantage of delayed onset of action (about 2weeks; Kakara et al., 2014; Koskinas et al., 2018). Genetic polymorphism associated with statin-induced myopathy in Chinese coronary artery disease patients (Liu et al., 2017). Several studies have demonstrated that using a higher dose of statin can easily induce liver injury (Alsheikh-Ali et al., 2007; Kasliwal et al., 2007; Chen et al., 2014; Naiqiong et al., 2017; Bandyopadhyay et al., 2018).

To achieve the target reduction in LDL-C, combinatory therapy using non-statin agents added to statin has been developed. Several recent trials have shown that the addition of either ezetimibe or anti-proprotein convertase subtilisin/kexin type 9 (PCSK9) monoclonal antibodies to statin therapy provides a further reduction in ASCVD risk, which is positively correlated with the incrementally achieved absolute LDL-C reduction (Giugliano et al., 2017, 2018; Schwartz et al., 2018; Koskinas et al., 2019). Current guidelines or expert advice have further recommended using PCSK9 inhibitors for high-risk or very high-risk patients given that the ezetimibe added to statin therapy failed to achieve the target LDL-C level. In the 2019 ESC/EAS Guidelines for the management of dyslipidemias (Mach et al., 2019), it is stated that for secondary prevention, patients at very high risk not achieving their goal on a maximum tolerated dose of statin and ezetimibe, a combination with a PCSK9 inhibitor is recommended. In the China cholesterol education program (CCEP) expert advice for the management of dyslipidemias to reduce cardiovascular risk (2019; China Cholesterol Education Program Working Committee et al., 2020), it is recommended to add PCSK9 inhibitors if the LDL-C goal of <55mg/dl (<1.4mmol/L) is not achieved after 4–6weeks of statin combined with ezetimibe therapy. In addition, for patients who may fail to achieve LDL-C<55mg/dl (<1.4mmol/L) with the ezetimibe added to statins therapy, PCSK9 inhibitors added to statins can be applied directly.

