### Sample Size Calculation

This is a superiority trial, and the sample size calculation is based on the primary efficacy endpoint, namely the percentage of change in LDL-C levels from baseline to week 4 after randomization. In order to have 90% power to detect clinically meaningful differences in treatment effects with a one-sided significance level of 5% (α=0.05), a sample size of 193 patients is required for each treatment arm. Assuming that the drop-out rate is 20%, this study aims to enroll approximately 484 patients, with 242 patients in the evolocumab plus statin arm and 242 in the statin-only arm. Therefore, the proposed study is expected to enroll a total of 500 patients with acute phase ACS, with 250 patients in each treatment arm.

The number of patients enrolled from each hospital is based on the bed size of each hospital. The Tianjin Chest Hospital plans to enroll 220 patients, and the remaining seven hospitals each will enroll 40 patients.

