### Statistical Analysis

The primary efficacy analysis will be based on the time from randomization assignment to the first occurrence of any component of MACE. Data will be analyzed using intention-to-treat analysis (ITT) and per protocol (PP) to assess the efficacy and safety of evolocumab in combination with moderate-intensity statin therapy. The superiority of evolocumab will be assessed for all efficacy endpoint. Continuous variables with an approximately normal distribution will be reported with mean±standard deviation (mean±SD), and differences between the two treatment arms will be tested using independent sample t-test. For continuous variables that are not normally distributed, the median and interquartile range (IQR) will be given, and the nonparametric Mann–Whiney U test will be conducted to test for differences between treatment arms. Discrete variables will be reported with counts and percentage for each arm, and differences between arms will be examined using Fisher’s exact test. In order to compare MACE differences, Kaplan–Meier survival curve analysis will be performed, and hazard ratio (HR) and 95% CI will be calculated. Log-rank tests will also be performed to evaluate the differences in significance and verify treatment efficacy.

The ITT population will include all randomized patients and the PP population will include all randomized patients who complete the entire study. Subjects with missing data will be excluded from the corresponding analysis. Logistic regression will be used to analyze differences in the central effect sizes.

Results of the proposed study will be analyzed using SAS 9.2 or higher version (SAS Institute, North Carolina, United States) software. All statistical tests will be two-tailed unless otherwise indicated or presented with a 95% confidence interval (CI), and statistical significance will be established as *p*<0.05.

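### Safety is analysed on all randomised patients and on completers only; the completer set drops patients taken off study for harm, and no set follows treatment received

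*Protocol article*

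**What the plan says.** Three sections of the protocol article bear on this.

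- Safety Evaluation: "Adverse events (AEs) will be recorded and summarized using descriptive statistics", and "incidence of AEs and/or serious adverse events (SAEs) will be summarized for each randomized treatment group". It adds: "For safety outcome analysis, missing data will not be imputed".
- Statistical Analysis: "Data will be analyzed using intention-to-treat analysis (ITT) and per protocol (PP) to assess the efficacy and safety of evolocumab". The sets are defined as follows: "The ITT population will include all randomized patients and the PP population will include all randomized patients who complete the entire study". It also says: "Subjects with missing data will be excluded from the corresponding analysis".
- Study Termination: the researchers end a patient's participation for, among other reasons, poor adherence, serious adverse drug reactions, loss to follow-up and other safety reasons. The same section asks for follow-up of adverse events that lead to withdrawal, and for assessments of withdrawn patients at the end of the study.

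Safety is part of the overall purpose given under Aims of the Study. No section names a safety set based on the drug a patient actually received.

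**The concern.** A completer set is a poor basis for safety whenever harm is a reason for not completing. Here it is one by rule: a patient who has a serious reaction to the drug and is terminated for it cannot be in PP, so that event cannot appear in one of the two named safety analyses. If such exits are commoner on evolocumab, the PP table makes that arm look safer than it was.

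The ITT table keeps these patients but has a different, smaller weakness. Dilution toward no difference is cautious in a superiority test of efficacy; for safety it leans toward finding no harm. Evolocumab patients never injected, and any controls who started a PCSK9 inhibitor, would pull the two arms together.

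At stake is how far either table can answer the trial's own safety question.

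**Working it through.** **1. The plan's own drop-out figure.** From Sample Size Calculation: 193 evaluable per arm and 20% drop-out. 193 / (1 − 0.20) = 241.25, rounded up to 242 per arm and 484 in total, as stated. Enrolment is then set at 500, or 250 per arm.

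**2. How many patients PP can omit.** 0.20 × 250 = 50 per arm, leaving 200. This is an upper figure for patients lost through harm, because the 20% covers all reasons for leaving.

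**3. What the omission can do.** Let N be the patients in an arm, E those with a given adverse event, L the leavers and x the leavers with the event. The completer risk is (E − x) / (N − L). It equals the true risk E/N only if x/L = E/N, and it is too low when leavers have the event more often than the arm as a whole.

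Illustration with assumed risks of 20% on evolocumab and 10% on control, so E = 50 and 25, with N = 250 and L = 50. Control leavers are taken as representative (x = 5), giving 20/200 = 10%. The values of x on evolocumab are also assumed:

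| Evolocumab leavers with the event (x) | Completer risk | Difference from control |
|---|---|---|
| 10 (representative) | 40/200 = 20% | 10 points (true value) |
| 20 | 30/200 = 15% | 5 points |
| 30 | 20/200 = 10% | 0 points |

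For an event that always leads to termination, x = E and the completer risk is zero by construction.

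**4. Dilution in the assigned-arm table.** Let u be the never-dosed share on evolocumab and c the share of controls starting a PCSK9 inhibitor. Assume that undosed patients carry the control risk and crossovers the drug risk. The observed difference is then the true difference × (1 − u − c). With risks of 20% and 10%:

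- u = 2%, c = 0: 19.8% − 10.0% = 9.8 points (98% retained)
- u = c = 5%: 19.5% − 10.5% = 9.0 points (90% retained)
- u = c = 10%: 19.0% − 11.0% = 8.0 points (80% retained)

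The documents give neither u nor c. At zero for both there is no dilution.

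**5. Early termination, if incidence means a simple percentage.** Assume a constant hazard and leavers observed for half of follow-up. A risk p becomes (1 − w)p + w(1 − √(1 − p)) when a share w leaves. With risks of 20% and 10%:

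- 20% leave in both arms: 18.1% against 9.0%; difference 9.1 points (91% retained), ratio 2.01
- 20% leave on evolocumab only: 18.1% against 10.0%; difference 8.1 points (81% retained)
- 20% leave on control only: 20.0% against 9.0%; difference 11.0 points (110%, an inflation)

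The direction therefore depends on which arm loses more follow-up. Balanced loss leaves the ratio nearly intact but still shrinks the risk difference by about a tenth.

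**The case against.** The strongest reply is that the article fixes less than a critical reader might infer.

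- **Crude counting.** One might infer that adverse events are counted crudely per randomised patient, with early leavers treated as fully observed. The text does not say so. It speaks of incidence and descriptive statistics, bars imputation, and excludes subjects with missing data from the analysis concerned, so the denominator is open. Study Termination also offsets part of the loss through its follow-up of events that lead to withdrawal.
- **Crossover.** One might infer that controls will start PCSK9 inhibitors, because the Introduction cites advice that "PCSK9 inhibitors added to statins can be applied directly" in some patients. That is background and not a trial rule. Prior use is an exclusion criterion, and no section describes use by controls during follow-up.
- **Never-dosed patients.** Evolocumab is planned within 72 hours of diagnosis, so nothing points to a sizeable undosed share.
- **Randomised-group reporting.** The sentence on randomised groups opens with clinical endpoints, and the serious adverse events listed next begin with cardiovascular events. For those, reporting by randomised group is defensible.
- **Detail left to the SAP.** Exposure-adjusted rates and the display of events after crossover commonly sit in an analysis plan, which is not shown.

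All of this stands, and it limits the point. It does not answer the stated rule that safety is assessed on completers, nor that both named safety sets ignore treatment received. An unseen plan could add a treated set, but the Statistical Analysis sentences would still need changing.

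**Conclusion.** The concern holds in a narrow form. The article assigns safety to all randomised patients and to completers, by randomised arm. Its own termination rules make the completer set exclude patients partly because of harm, up to about 50 of 250 per arm at the planned drop-out. That analysis can understate drug harm; by how much depends on how many leave through harm and in which arm, which the documents do not say.

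The dilution in the assigned-arm table is arithmetically certain for any given share of never-dosed and crossover patients, but that share is unknown and may be small. A general claim that the safety comparison is biased toward no harm is not supported: early termination can shift crude incidence either way, and the article does not settle how incidence is computed. The point is minor, a wording correction to a stated rule.

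**What to change.** - In Statistical Analysis, limit PP to efficacy and remove it from safety.
- Define the main safety set as all patients with at least one dose of study treatment, grouped by treatment received. Since both arms take a statin, state that a patient counts as evolocumab only if at least one injection was given.
- Keep the randomised-group table of Safety Evaluation as supportive.
- Optionally, show exposure-adjusted rates beside the percentages, because unequal early termination could bias crude incidence in either direction. This, and the display of events after any crossover, can be left to the SAP.

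The cost is a few sentences and one more table. Treatment Procedures Records already has all medication recorded, so identifying treatment received should need no new collection; the article does not say whether start and event dates are captured, and exposure-adjusted rates would need them. The treated set is not fully protected by randomisation, which is why the randomised-group table stays beside it.

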Monoclonal antibodies target to PCSK9 are relatively novel lipid-lowering agents that have benefits in reducing the risk of cardiovascular disease (Giugliano et al., 2017; Schwartz et al., 2018; Koskinas et al., 2019). To date, two different anti-PCSK9 antibodies have been approved and used in clinical trials to investigate the efficacy of reducing LDL-C levels in other ethnic populations. In the FOURIER trial (Giugliano et al., 2017), the investigators conducted a multinational study where a total of 25,982 patients with clinically evident vascular diseases were randomized into the evolocumab and the matching placebo groups on a background of high-intensity statin therapy. The authors found that patients achieved progressively lower LDL cholesterol concentrations at 4weeks from baseline had progressively fewer cardiovascular events with no increase in adverse events. Moreover, they demonstrated that lowering LDL-C to well below the recommended level in current guidelines (e.g., <0.5mmol/L) is safe for the highest-risk patients. In the EVOPACS trial (Koskinas et al., 2019), the investigators tested the feasibility, safety, and LDL-C-lowering efficacy of evolocumab on top of atorvastatin in European ACS patients for early reduction of LDL-C levels. The results showed a significant reduction of LDL-C at week 8 in the evolocumab group as compared with the placebo group. Moreover, compared with placebo, evolocumab may further benefit patients as evolocumab significantly reduced other atherosclerotic lipid particles, including total cholesterol, apolipoprotein B, non-HDL-C, triglycerides and lipoproteins(a). In ODYSSEY OUTCOMES trial (Schwartz et al., 2018), another type of anti-PCSK9 antibody, alirocumab, was used. Despite different design, the ODYSSEY OUTCOMES study suggested that the risks of any coronary heart disease event, major coronary heart disease events, any cardiovascular event, and a composite of death from any cause, nonfatal myocardial infarction, or nonfatal ischemic stroke were lower among patients treated with alirocumab than among those who received placebo. The authors concluded that alirocumab added to intensive statin therapy reduces cardiovascular morbidity and mortality after ACS. Compared with these studies, our trial design will use evolocumab added to moderate-intensity statins instead of high-intensity statins and will focus on the Chinese population because using a higher dose of statin can easily induce liver injury and myopathy.

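### Whole classes of event (muscle-related, neurocognitive, new diabetes) count as serious adverse events whatever their seriousness, and liver injury is not named in any safety list

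*Protocol article*

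**What the plan says.** All of the classification is in the Safety Evaluation section of the protocol article.

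- The SAE list opens with cardiovascular events: "Serious adverse events include cardiovascular events (death, fatal or non-fatal MI, coronary revascularization, hospitalization for recurrent ACS, hospitalization for heart failure, stroke, transient ischemic attack".
- The same list continues with three non-cardiovascular classes, and the next category follows after the semicolon: "muscle-related adverse events, neurocognitive impairments, incident diabetes; adverse events of special interest include allergies, injection-site reactions, or any other clinical abnormalities". No grade, laboratory threshold, hospitalisation or other condition is attached to the three classes.
- The categories feed the safety summary: "incidence of AEs and/or serious adverse events (SAEs) will be summarized for each randomized treatment group".
- They also drive reporting: "If unexpected or SAE occur, the researchers or staff will fill out the SAE Report Form and notify the Ethics Committee". The sentence goes on to the national drug regulator and other authorities.

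On the liver, the Introduction states: "Several studies have demonstrated that using a higher dose of statin can easily induce liver injury". The Discussion explains the choice of moderate-intensity statin "because using a higher dose of statin can easily induce liver injury and myopathy", and the Abstract makes the same point in its background. Table 1 schedules liver function tests at screening, day 7 and weeks 4, 12, 24 and 48.

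**The concern.** Seriousness is a property of the individual event: what it did to the patient. The article assigns it by type of event for three classes that range from trivial to grave. Muscle complaints are the clearest case.

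Two uses of the category are affected. The SAE incidence per arm would mix minor complaints with deaths, infarctions and hospitalisations, so a reader could not take it as a rate of serious harm. The notification route would also carry minor events alongside those that it exists to bring forward.

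The special-interest category has a related weakness. It names two types of event and then admits anything else, so it singles out little. Liver injury and myopathy are cited together as the reason for the statin intensity. Muscle events have a named place in the safety section, but liver injury has none.

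**Working it through.** **Text check**

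| Item | Where it is placed | Condition attached |
|---|---|---|
| Cardiovascular events | SAE list | Several carry their own (death, hospitalisation) |
| Muscle, neurocognitive, new diabetes | SAE list | None |
| Allergies, injection-site reactions | Special interest | None |
| Liver injury | Not named as an SAE, as special interest or among intervention-related complications | Falls under the special-interest catch-all |
| Liver tests | Table 1, six time points | Not applicable |

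The article gives no adverse event rate, so there is no figure to reproduce. The only document input below is 250 patients per arm (Sample Size Calculation). All rates are assumptions, chosen to show direction and range.

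**1. Inflation of the count.** Let *m* be the rate of non-serious muscle events, *s* other non-cardiovascular serious events and *c* cardiovascular SAEs, with no overlap. The non-serious share of SAEs is *m*/(*m*+*s*+*c*). With *s* = 3% (7.5 per 250):

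| *m* | *c* = 10% (25 per 250) | *c* = 20% (50 per 250) |
|---|---|---|
| 2% (5) | 5/37.5 = 13% | 5/62.5 = 8% |
| 5% (12.5) | 12.5/45 = 28% | 12.5/70 = 18% |
| 10% (25) | 25/57.5 = 43% | 25/82.5 = 30% |

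**2. Equal muscle events in both arms.** With independence, the recorded SAE risk is 1 − (1 − *p*)(1 − *m*), where *p* is the true serious risk. Take *p* = 10% and 5% in the two arms. Power is the normal approximation for a two-sided 5% test, used only as a gauge of lost information.

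| *m* | Recorded risks | Ratio | Difference | Power, 250 per arm |
|---|---|---|---|---|
| 0% | 10.0% vs 5.0% | 0.50 | 5.0 points | 56.5% |
| 2% | 11.8% vs 6.9% | 0.58 | 4.9 points | 46.9% |
| 5% | 14.5% vs 9.75% | 0.67 | 4.75 points | 36.9% |
| 10% | 19.0% vs 14.5% | 0.76 | 4.5 points | 27.0% |

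The ratio moves towards 1. The absolute difference shrinks only by the factor (1 − *m*), so the lost power comes mostly from added noise.

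**3. No true difference in serious events** (*p* = 7% in both arms).

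- Muscle events 5% vs 5%: 11.65% vs 11.65%, ratio 1.00.
- Muscle events 5% vs 8%: 11.65% vs 14.44%, ratio 1.24.
- Muscle events 5% vs 10%: 11.65% vs 16.30%, ratio 1.40.

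A false difference in SAEs appears only when muscle events are recorded at different rates in the two arms.

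**The case against.** **The article is condensed, and the verb *include* leaves the list open.** A general definition of seriousness may stand in the full protocol or on the SAE form, and its absence here is no finding. That is right, but it does not settle the point. The article positively places three event classes on the SAE list, and neither an open list nor a further definition takes them off it.

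**A reader might infer that the comparison between arms is distorted.** The article does not support that. One definition applies to both arms, both take the same statin options, and adverse events are to be summarised descriptively. Equal reporting dilutes a true difference and leaves a null one at 1.00. Unequal reporting of subjective symptoms is possible in an open-label trial, but nothing shows that it will occur.

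**A reader might infer that liver harm is left out or cannot be reported.** That also goes too far. The catch-all takes in a liver abnormality, all adverse events are recorded, and enzymes and bilirubin are measured at scheduled visits. Moreover, the rationale ties liver injury to higher statin doses, which neither arm receives, so it is not the harm that randomisation contrasts. What stands is that liver injury is not named.

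**A reader might infer that most recorded SAEs would be non-serious.** Assumed rates of 10% and 3% give 25/32.5 = 77%, but only by leaving out the cardiovascular events that the same list contains. With these included, the assumed range is 8% to 43%.

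**The special-interest category is not empty.** It names allergies and injection-site reactions. The fault is that its last entry has no limit.

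**Conclusion.** The point holds as a classification error. Followed as written, the Safety Evaluation section produces an SAE count that includes events that are not serious, and it sends those events through the notification route. The consequence for the arm comparison is dilution. Bias would need different reporting by arm, which remains a possibility only. Liver injury is covered by the catch-all and by scheduled tests, but no safety category names it.

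The size cannot be fixed from the article. The shares, ratios and power above rest wholly on assumed rates, independence or absence of overlap, and 250 patients per arm. The conclusion needs none of them, since it follows from the wording. No primary or secondary efficacy result depends on this category. The correction is worth making because it is cheap and makes the SAE incidence interpretable.

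**What to change.** - Classify any event, of whatever type, as an SAE by standard seriousness criteria: death, life-threatening, hospitalisation or its prolongation, lasting disability, or medically important.
- Move muscle-related events, neurocognitive impairment and new diabetes to the named events of special interest. Each is then also an SAE only when it meets a seriousness criterion.
- Add liver injury to that list, derived from the AST, ALT and bilirubin results already scheduled. The investigators should set the threshold.
- Delete the catch-all. Other abnormalities remain recorded as ordinary adverse events.
- Optionally, show SAEs with and without the MACE components. If so, state which definition is used: MACE counts only unplanned revascularisation, whereas the SAE list counts coronary revascularisation without that limit.

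The cost is protocol and CRF wording, with a seriousness item for each event. No new visit or laboratory test is needed. Events already reported under the present list would need to be recoded for seriousness.
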